### Assignment of interventions

#### Sample size calculation

A total of 48 breastfeeding HIV exposed uninfected eligible neonates will be enrolled in the study (8 neonates recruited in each arm). Power calculations were not performed for this study, given that it is a Phase 1 trial aiming to test safety and PK in a small number of participants [12]. The trial objectives specifically state an evaluation of safety that did not include comparing safety between arms; thus there was no need to perform power calculation. We have, however, carefully evaluate and presented the probability of observing at least one event under various hypothetical SAE rates and this forms the key sample size consideration. The enrolment of 48 neonates will allow the study to have 8 infants per arm (target sample size of each arm is 6) in the final safety dataset in the hypothesis of a 25% of lost to follow-up.

The probabilities reported in Table 6 highlight the likelihood of the study to detect either rare or common SAEs (Table 6). According to the reported probabilities, there is 11% chance of getting 2 SAEs in a sample of 8 participants when the true SAE proportion is 50% (i.e. common) and 5% when the true SAE proportion is 5% (i.e. rare). In addition, there is 0.4% chance of getting 0 (no) SAEs in a sample of 8 participants when the true SAE proportion is 50% (i.e. common) and 66% when the true SAE proportion is 5% (i.e. rare).

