#### Descriptive and univariate analyses

All the available safety data of each participant will be considered in the analyses; these data will be classified as severity (grade), expectedness, and potential relatedness (causality) to the study intervention. Descriptive analyses will be performed according to the study arm and the endpoints will be summarized using means with standard deviations or medians with interquartile ranges or ranges or 95% confidence intervals (CI) for quantitative variables, and proportions with their 95% CI for qualitative or categorical variables; CIs will be calculated using the exact method.

Given the small sample size of the study arms, there will be no statistical power for a formal test of differences between study arms with respect to safety. The analyses will check for clinically relevant differences in the main baseline maternal and infant characteristics between the following study arms: 2 vs 3, 4 vs 5, 6 vs 3 and 5; the presence of relevant imbalances in these characteristics among arms will be eventually tested by calculating differences [between means (standardised effect size) or proportions] with the corresponding 95% confidence intervals.

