#### Secondary analyses on secondary endpoints

AEs rates, expressed as number of events divided by number of person-days of follow-up and calculated by univariate Poisson regression, will be also estimated among enrolled neonates.

Pharmacokinetic parameters will be estimated by a non-compartmental analysis (NCA) performed using WinNonlin® version 8.0 (Certara, St. Louis, MO, USA) applied on data collected from neonates who completed the study. The primary PK endpoints will be: clearance, maximum plasma concentration (C_max_) and area under the concentration–time curve (AUC) from time zero to the last quantifiable time point (AUClast). C_max_ values will be compared with those at baseline (pre-administration of bNAbs) using the Wilcoxon signed-rank test. Bioequivalence between study arms will be assessed using the geometric mean ratio (GMR) and 90% confidence interval (90% CI) of AUClast and C_max_. The conventional bioequivalence criterion of 0.80 will be used.

The other endpoints of the trials will be summarized with descriptive analyses; they will be described according to the study arm and, if assessable, by month of follow-up until a maximum of 6 months since first or second bNAbs administration, using means with standard deviations or medians with interquartile ranges or ranges or 95%CI for quantitative variables, and proportions with their 95% CI for qualitative or categorical variables. Non-parametric tests that will be considered to test changes in continuous measures during follow-up are: Wilcoxon signed-rank test or Friedman test.

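### Adverse event rates are to come from plain Poisson regression with no allowance for dependence of events within an infant; if events cluster, their standard errors and intervals are too narrow.

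*Protocol article*

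**What the plan says.** Under *Secondary analyses on secondary endpoints* the protocol article specifies AE rates as events over person-days, "calculated by univariate Poisson regression", and says that these "will be also estimated among enrolled neonates". The numerator is a count of events, not of infants. No infant-level term, robust variance, dispersion parameter or alternative count model is named.

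Under *Descriptive and univariate analyses* it adds that "All the available safety data of each participant will be considered in the analyses", so repeat events in the same infant enter the count. The general rule for intervals in that section is "proportions with their 95% CI for qualitative or categorical variables; CIs will be calculated using the exact method". No interval is expressly stated for the AE rates.

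Follow-up for the secondary summaries runs "until a maximum of 6 months since first or second bNAbs administration". Tables 4 and 5 schedule the safety assessment (full blood count with differential and platelets, ALT, AST, total bilirubin, creatinine) at entry and at every later visit.

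**The concern.** A Poisson model takes the variance of the event count to equal its mean. That holds if events arise independently at the same rate in every infant. It fails if one event makes another more likely in the same infant, for example a laboratory abnormality that persists or recurs over several scheduled tests, or if some infants are more prone to AEs than others. The variance then exceeds the mean, and the model-based standard error is too small by the square root of the variance/mean ratio.

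At stake is how precise the AE rates appear. Safety up to 6 months is a stated secondary objective. With 8 infants per arm, an interval that treats every event as independent information can make a small cohort look better characterised than it is.

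**Working it through.** **Inputs from the document.**
- Infants per arm: 8. The article's own figures reproduce: a target of 6 with 25% loss gives 6/(1 − 0.25) = 8, and 6 groups × 8 = 48.
- Post-entry visits with safety laboratory tests, Table 4 (arms 1 to 5): days 3, 14 and 28 plus months 2 to 6 = 3 + 5 = 8.
- The same, Table 5 (arm 6/6b): days 1, 3, 14, 28, 56 and 84 after the first administration, days 1, 3, 14 and 28 after the second, then months 2 to 6 = 6 + 4 + 5 = 15.
- No figure is given for the AE rates or their precision, so there is none to reproduce.

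**Assumptions, not in the document.** Mean of 3 or 6 AEs per infant, equal follow-up, and a variance/mean ratio φ between 1 and 3, generated by gamma-Poisson counts.

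**Formula.** With Y events in total, the Poisson standard error of the log rate is 1/√Y. The true one is √(φ/Y). A nominal 95% interval on the log scale therefore covers approximately 2Φ(1.96/√φ) − 1, where Φ is the standard normal distribution function.

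**Results, 8 infants, 40,000 simulated arms per setting.**

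| φ | Formula | Simulated, log-Wald Poisson | Simulated, exact Poisson |
|---|---|---|---|
| 1 | 95% | 95% | 96% |
| 1.5 | 89% | 89% | 90–91% |
| 2 | 83% | 83–84% | 85–86% |
| 3 | 74% | 74–75% | 76–77% |

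- With 6 infants, log-Wald coverage is 83–85% at φ = 2 and 74–77% at φ = 3.
- Pooling does not cure it. With a mean of 3 events, log-Wald coverage at φ = 1.75, 2.5 and 4 is 86%, 79% and 68% for 8 infants, and 86%, 78% and 68% for 48.
- If events are few and variation is mild (mean 1, φ = 1.25, 8 infants), coverage is 93% (log-Wald) and 95% (exact), so little is lost.

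**What it means for one arm.** Take 8 infants with 3 AEs each on average, so Y = 24.
- Poisson: 1.96/√24 = 0.400, so the limits are the rate divided and multiplied by exp(0.400) = 1.49.
- φ = 2 with the t quantile on 7 degrees of freedom: 2.365 × √(2/24) = 0.683, so the factor is exp(0.683) = 1.98.

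**Infant-level alternatives, 8 infants.**
- A robust variance with a t quantile on n−1 degrees of freedom covers 92% to 97.5% over assumed means of 1, 3 and 6 and φ from 1 to 13. Plain Poisson covers 41% to 95% (log-Wald) or 42% to 97% (exact) over the same settings.
- A Pearson-scaled variance with dispersion floored at 1 and the same t quantile covers 95–97% at φ = 2 to 3, and is 1.6 to 2.0 times as wide as the Poisson interval on the log scale. At φ = 1 it covers about 98.7% and is 1.3 times as wide.

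**The case against.** *No interval is promised for these rates.* This stands as a limit on the point: the text says only that rates will be estimated, and events over person-days is the same number under any variance. But a single rate needs no regression. What the regression adds is a standard error and an interval, and the article's general practice is to attach 95% intervals to its summaries.

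*The analysis plan, not shown, may specify a robust variance.* It may, and the words used do not exclude one. The point is not the missing detail, though. The protocol names a specific model whose default error is vulnerable here, and the article's exact method for intervals does not repair it.

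*Several events per infant are compatible with a Poisson model.* Correct. A reader might infer that the intervals must be too narrow because infants contribute repeat events. The document does not support that: at φ = 1 coverage is about 95%, and neither φ nor the AE frequency can be derived from it.

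*The rates are peripheral.* Largely correct. A reader might take them for the main longer-term safety summary, but *Secondary endpoints* lists the frequency of participants with any AE and the frequency or proportion with at least one, and clustering does not affect such per-infant measures. A reader might also fear that chance differences between doses will look real. The article plans no safety comparison between arms (*Sample size calculation*; *Descriptive and univariate analyses*) and ties no decision to the rates.

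**Conclusion.** The point holds conditionally. The stated method makes no allowance for extra-Poisson variation. Repeated laboratory testing of the same infants makes such variation plausible, but its size is unknown. Under the assumed 3 to 6 AEs per infant, a nominal 95% interval would cover 83–84% if the variance is twice the mean and 74–75% if it is three times the mean. There is no shortfall if the two are equal. Exact Poisson limits gain only about two percentage points, and more infants do not help.

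The consequence is confined to the precision of a descriptive secondary summary. The rates themselves, the per-infant primary endpoint, the per-infant secondary proportions, the stopping triggers and the sample size are not touched. It is worth correcting because the remedy is cheap, not because a main conclusion is at risk.

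**What to change.** Add one line to *Secondary analyses on secondary endpoints*, or to the analysis plan before analysis, along these lines: any 95% confidence interval for an AE rate will treat the infant as the unit, using the Poisson model with an infant-level robust variance and a t quantile on n−1 degrees of freedom, n being the number of infants in the group; where a group has no events, an exact Poisson limit will be given (upper two-sided 95% limit 3.69 divided by person-days).

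A Pearson dispersion-scaled variance, floored at 1, with the same t quantile is an acceptable alternative. The choice should be fixed in advance. The floored version is clearly conservative without clustering (about 98–99% coverage). The robust version stays near 95% there (95% at a mean of 3 events), but can fall to about 92% under extreme clustering. It also collapses to zero width if every infant has the same observed rate, in which case the floored version should be used.

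The cost is the wording and wider intervals. Design, data collection and safety monitoring do not change.

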The ambitious goal to eliminate new pediatric HIV infections by 2030 requires accelerated prevention strategies in high-risk settings. Several approaches could be pursued. In contrast with adult individuals at high risk of HIV acquisition, the universal and equitable access to pre-exposure prophylaxis (PreP) is so far not available to children [4], despite clinical trial evidence.

Innovative biomedical solutions, including long-acting, injectable formulations, offer a paradigm shift in the pediatric HIV epidemic [5]. Modified HIV-1 bNAbs are highly potent and long-acting, and therefore have the indisputable potential for preventing MTCT perinatally and postnatally. Indeed, bNAbs for infant prophylaxis were identified as a potentially safe and durable option by the WHO-led “Paediatric Antiretroviral Drug Optimization group” and as a priority for drug development [6].

On the basis of modelling data available we propose to test the antibody directed to the CD4-binding site (CD4-bs e.g. VRC07-523) and combine it with an antibody to the V2-glycan supersite (CAP256V2). Many of the bNAbs have been engineered to enhance their therapeutic potential. Modification of the Fc-region of the bNAbs by an “LS” mutation increases binding to neonatal Fc-receptors, improving protection against lentiviral infection in non-human primates [7] and extending the bNAbs half-life to 4–6 months in adults [8]. Furthermore, isolation of more potent bNAbs (e.g. CAP256V2LS) [9] and engineering of bNAbs to increase potency (e.g. VRC07-523LS) [10] has made subcutaneous (SC) administration a realistic option in neonates and infants. Such extended half-life and elevated potency would enable protection of breastfeeding infants during the first year of life with as few as 2–3 administrations. In addition, they become particularly interesting as the volume of each administration would not exceed 1.5 ml, given the high bNAb concentration in formulations (100–150 mg/ml).

The aim of our study is to define the optimal dose(s), the ideal combination(s) of bNAbs (potency and breadth) and timing of SC administration to prevent infant HIV acquisition from birth and through breastfeeding in high-incidence countries such as South Africa.

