## Methods

### Study products

In this protocol the bNAbs CAP256V2LS, never tested in pediatric populations, and VRC07-523LS were chosen based on the following characteristics:epitope complementarity (CD4bs and V1V2-glycan) to target different viral regions involved in cell entry;breadth for subtype C (dominant in South Africa) and other subtypes to cover also viruses circulating in other high prevalent areas beside South Africa;half-life > 3–4 months in adults (VRC07-523LS), allowing large administrations intervals with the goal of providing the least number of administration during the breastfeeding period;potency and availability of the formulation for SC administration, which in children is preferable to intravenous administration;CAP256V2LS safety assessment in adults (CAPRISA 012B trial) showed no serious adverse events, and adverse events did not result in study product discontinuation;VRC07-523LS safety assessment in the IMPAACT P1112 phase I pediatric study showed that the product is generally well tolerated, none of the severe adverse events reported were related to the study product or resulted in study product discontinuation in any participant.availability through non-profit partnerships and a Target Product Profile plan to reduce costs of production.

The Vaccine Research Center (VRC), National Institute of Allergy and Infectious Diseases (NIAID), National Institutes of Health (NIH) developed VRC07-523LS, while CAP256V2LS has been developed by VRC, together with Centre for the AIDS Programme of Research in South Africa (CAPRISA). The VRC, NIAID, NIH is the sponsor of the original U.S. Food and Drug Administration (FDA) investigational new drug application (IND) to evaluate the potential clinical uses of CAP256V2LS and VRC07-523LS.

CAP256V2LS and VRC07-523LS are both recombinant human immunoglobulin G1 (IgG1) antibody produced in the Chinese Hamster Ovary (CHO) DG44 cell line in accordance with the current Good Manufacturing Practice (cGMP) regulations. The VRC Pilot Plant-VCMP is a qualified manufacturer for the release of Investigational Medicinal Products and labels clinical vials for the trial, and it manufactured, tested and released the master cell bank. Both products are approved for use in South Africa under clinical trial conditions. Neither product is subject to agreement with companies or other organizations for supply of the products.

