##### Secondary objectives

To evaluate the PK profile up to 6 months of each single bNAb administered, at different doses within 96 hours of birth in breastfeeding HIV exposed neonates born without HIV (arms 1 through 5).To evaluate the PK profile up to 3 months of bNAbs administered in combination, at different doses within 96 hours of birth in breastfeeding exposed neonates without HIV (arm 6).To evaluate the PK profile up to 6 months of each bNAb, administered in combination, in breastfeeding exposed neonates without HIV infants after a second administration at 3 months (arms 6/6b).To assess safety (AE) up to 6 months after each single bNAb (arms 1 to 5), up to 3 months after the first combined bNAbs administration (arm 6) and up to 6 months after the second administration of the combined bNAbs (arm 6b).

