##### Secondary endpoints

PK curve of each single bNAb.Clearance, C_max_, area under the curve (AUC) and elimination half-life of each single bNAb.Frequency/proportion of children above the target bNAb plasma concentration (IC80) determined by in vitro studies for each bNAb.Frequency of participants with any type of AE including local and systemic reactions, laboratory toxicities, and/or clinical events, any time from the first day of study product administration up to 6 months after each single or combined bNabs administration.Frequency/proportion of participants who develop at least 1 AE including local and systemic reactions, laboratory toxicities, and/or clinical events, any time from the first day of study product administration up to 6 months after each single or after the combined second bNabs administration.Frequency/proportion of new HIV-1 infection among neonates/infants.

The exploratory objectives and endpoints have been omitted in this paper for brevity.

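### On the adult half-lives the protocol quotes, NCA clearance and half-life would lean heavily on extrapolation, and single-dose NCA fits the arm 6/6b data badly

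*Protocol article*

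**What the plan says.** **Method and parameters.** The protocol article, under Secondary analyses on secondary endpoints, states "Pharmacokinetic parameters will be estimated by a non-compartmental analysis (NCA"), run on infants who completed the study. It continues: "The primary PK endpoints will be: clearance, maximum plasma concentration (C_max_) and area under the concentration–time curve (AUC"), with AUC taken to the last quantifiable sample (AUClast). The Secondary endpoints list adds "area under the curve (AUC) and elimination half-life of each single bNAb".

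**Observation windows (Secondary objectives).**
- Arms 1–5: "To evaluate the PK profile up to 6 months of each single bNAb administered".
- Arm 6, first dose: "To evaluate the PK profile up to 3 months of bNAbs administered in combination".
- After the second dose: "To evaluate the PK profile up to 6 months of each bNAb, administered in combination".

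Table 5 places the second administration on day 84. Table 1 shows that the amounts differ: 60 + 90 mg first, then 120 + 120 mg (CAP256V2LS + VRC07-523LS).

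**Expected half-life.** Background and rational describes the LS mutation as "extending the bNAbs half-life to 4–6 months in adults". Study products gives "half-life > 3–4 months in adults (VRC07-523LS"). Both are adult figures. The article gives no infant half-life and none specific to CAP256V2LS.

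**The concern.** After one subcutaneous dose, NCA clearance is the dose divided by AUC to infinity (an apparent clearance, CL/F). NCA half-life is ln 2 divided by a terminal slope fitted to each infant's late samples. Both need follow-up that is long relative to the half-life, and the quoted half-lives are about as long as the follow-up or longer.

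The trial aims to inform the timing of administration, and the Background's case for two or three doses in the first year rests on slow elimination. If clearance and half-life are mostly extrapolated, a reader could take them as measured properties of the antibodies in infants when they mainly reflect a short, noisy stretch of the curve. The combination arm is the most exposed: its first-dose window is the shortest, and its second-dose curve starts on top of the first.

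**Working it through.** The article states no figure for half-lives covered, AUC extrapolated or PK precision, so there is nothing of its own to reproduce.

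**1. Coverage and unobserved AUC.** Inputs: window T = 182 days (6 months) or 84 days; half-life h = 91, 122 or 183 days (3, 4 or 6 months), plus 61 days (2 months) as an assumed shorter infant value. Half-lives covered = T/h. Under mono-exponential decline with absorption ignored, the unobserved share of AUC to infinity is 2^(−T/h).

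| Half-life | Covered, T = 182 | Unobserved | Covered, T = 84 | Unobserved |
|---|---|---|---|---|
| 2 months (assumed) | 2.98 | 13% | 1.38 | 39% |
| 3 months | 2.00 | 25% | 0.92 | 53% |
| 4 months | 1.49 | 36% | 0.69 | 62% |
| 6 months | 0.99 | 50% | 0.46 | 73% |

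The VRC07-523LS figure is a lower bound (more than 3–4 months), so 2.00 is a ceiling: hence just under 2. Adding first-order absorption with an assumed 2-day absorption half-life moves the shares by about 1 percentage point.

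**2. Half-life needed to meet a limit.** Taking 20% as an illustrative limit (not in the protocol), 2^(−T/h) ≤ 0.20 requires h ≤ T/log2(5) = T/2.32. That is 78 days for T = 182 and 36 days for T = 84. Neither quoted half-life meets either value.

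**3. Precision of one infant's terminal slope.** For a log-linear fit, CV = σ/(k√Sxx), where k = ln 2/h and Sxx is the sum of squared deviations of the sampling times. Assumptions: samples at days 14, 28, 56 and 84, continuing every 28 days to day 168 for the 6-month window; residual SD on the log scale σ = 0.1 to 0.2; time in 28-day months.
- 6-month window: Sxx = 25.2. CV is 9–17% at a 3-month half-life and 17–34% at 6 months.
- 3-month window: Sxx = 3.69. CV is 0.1/(0.231 × 1.92) = 23% to 45% at 3 months and 45–90% at 6 months. In simulation, up to 13% of infants showed no decline at all (6-month half-life, σ = 0.2).

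**4. Carry-over into the second-dose curve.** Under the same model the fraction of the first dose remaining at day 84 is f = 53–73%, or 39% at a 2-month half-life. With linear kinetics and equal bioavailability, the first dose's share of AUC to infinity after the second dose is D1·f/(D1·f + D2).
- CAP256V2LS: 60 × 0.53 = 32 mg, and 32/152 = 21%; at f = 0.73, 44/164 = 27%. At a 2-month half-life, 23/143 = 16%.
- VRC07-523LS: 90 × 0.53 = 48 mg, and 48/168 = 28%; at f = 0.73, 66/186 = 35%. At a 2-month half-life, 35/155 = 22%.

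A single-dose NCA after the second dose that ignored this would understate clearance by those percentages. Subtracting the residue needs the first-dose slope, the poorly determined quantity in step 3.

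**The case against.** **The half-lives are adult values.** This stands, and it makes the result conditional. Growth dilutes antibody and shortens the apparent half-life. If distribution volume doubled in 4–6 months (an assumption), the unobserved share would be 2^−(T/h + T/doubling time): about 9–25% at 6 months, much of it under a 20% limit. For the first arm 6 dose it would still be about 33–53%.

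**Clearance and half-life are still estimable in arms 1–5.** This stands too. A reader might infer that the parameters cannot be delivered at all. Step 3 does not support that: over 6 months the slope is imprecise but usable.

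**No bias between arms follows from the text.** A reader might infer that clearance would seem to rise when the antibodies are combined, because less of the curve is seen. That holds only if clearance were computed as dose/AUClast. The protocol lists clearance and AUClast separately and does not say so. It plans no comparison of clearance between arms; its geometric mean ratios concern AUClast and Cmax, which need no extrapolation to infinity.

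**Separate first-dose parameters for arm 6 are not clearly promised.** This stands in part. The objective there is a PK profile to 3 months, and the endpoint's reference to each single antibody can be read as the single-antibody arms. But the NCA sentence is not limited to any arm.

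**Extrapolation limits belong in the SAP, and the timing question has other support.** Both are fair. The absence of an extrapolation rule is not the finding. The second-dose timing was settled in discussions informed by arms 1–5, and the share of infants above the IC80 target addresses the interval without extrapolation. What remains is that the article fixes a method and endpoints that suit the arm 6/6b data poorly.

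**Conclusion.** The point holds in conditional form. On the quoted adult half-lives, NCA clearance and half-life would rest on extrapolating about 25–50% of AUC to infinity in arms 1–5 and 53–73% after the first arm 6 dose. If infant half-life is nearer 2 months, arms 1–5 may be adequate, but the first arm 6 dose is still about 39% unobserved. The arm 6/6b problem therefore survives a much shorter half-life, and carry-over adds a second difficulty after day 84.

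This rests on mono-exponential decline, linear kinetics, and sampling at the scheduled visits with an assumed residual error. The primary safety endpoint, Cmax and the AUClast comparison do not depend on the extrapolation.

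**What to change.** In Secondary analyses on secondary endpoints:

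- Keep NCA for Cmax and AUClast.
- Estimate clearance and half-life, at least for arms 6/6b, with one population PK model per antibody. Use all concentrations, actual dose amounts and times, and body weight as a time-varying covariate. The model handles both doses jointly, so carry-over needs no separate correction.
- Where an NCA clearance or half-life is reported, base clearance on AUC to infinity, state the extrapolated fraction, and do not interpret either estimate above a fixed limit (for example 20%).
- Say whether separate parameters are intended for the first arm 6 dose.

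The cost is analysis wording and modelling time, with no new samples or visits. The downside is dependence on model assumptions: a model borrows information across arms and doses but adds no first-dose observations beyond day 84.

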**Methods:**

Two bNAbs, CAP256V2LS and VRC07-523LS, will be assessed in a sequential and randomized phase I, single-site, single-blind, dose-finding trial. We aim to investigate the 28-day safety and pharmacokinetics (PK) profile of incrementally higher doses of these bNAbs in breastfeeding HIV-1 exposed born without HIV neonates alongside standard of care antiretroviral (ARV) medication to prevent (infants) or treat (mothers) HIV infection.

The trial design includes 3 steps and 7 arms (1, 2, 3, 4, 5, 6 and 6b) with 8 infants in each arm. The first step will evaluate the safety and PK profile of the bNAbs when given alone as a single subcutaneous (SC) administration at increasing mg/kg body weight doses within 96 h of birth: arms 1, 2 and 3 at doses of 5, 10, and 20 mg/kg of CAP256V2LS, respectively; arms 4 and 5 at doses of 20 and 30 mg/kg of VRC07-523LS, respectively. Step two will evaluate the safety and PK profile of a combination of the two bNAbs administered SC at fixed doses within 96 h of birth. Step three will evaluate the safety and PK profile of the two bNAbs administered SC in combination at fixed doses, after 3 months. Arms 1 and 6 will follow sequential recruitment, whereas randomization will occur sequentially between arms (a) 2 & 4 and (b) 3 & 5. Before each randomization, a safety pause will allow review of safety data of the preceding arms.

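### The elimination half-life is to come from non-compartmental analysis in infants who grow fast from birth, so it will include dilution by growth and read too short

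*Protocol article*

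**What the plan says.** Under *Secondary analyses on secondary endpoints* the protocol article fixes one method for all PK parameters: "Pharmacokinetic parameters will be estimated by a non-compartmental analysis (NCA"). The same paragraph puts clearance first among the main PK quantities: "The primary PK endpoints will be: clearance, maximum plasma concentration (C_max"), with AUClast third. *Secondary endpoints* adds half-life: "Clearance, C_max_, area under the curve (AUC) and elimination half-life of each single bNAb". No sentence says outright that half-life comes from the non-compartmental analysis; that follows from reading the two sections together.

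In step 1 each antibody is "given alone as a single subcutaneous (SC) administration at increasing mg/kg body weight doses within 96 h of birth". The PK windows are in *Secondary objectives*: for arms 1 to 5, "To evaluate the PK profile up to 6 months of each single bNAb administered"; for arm 6, "To evaluate the PK profile up to 3 months of bNAbs administered in combination", followed by 6 months after the second dose at 12 weeks. Birth weight at entry is 2.0 to 4.0 kg. The article names no second PK method and no weight term in the PK analysis.

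**The concern.** Non-compartmental half-life is ln 2 divided by the terminal slope of log concentration. It equals elimination half-life only if volume is constant over the window. In an infant followed from birth, volume increases with body size, so concentration would decline even if no antibody were removed. Longer or more complete follow-up does not cure this.

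The effect is large here because elimination is expected to be slow. The background section describes the LS mutation as "extending the bNAbs half-life to 4–6 months in adults", and *Study products* gives more than 3 to 4 months in adults for VRC07-523LS. These times are as long as the growth period itself, so the two rates are of similar size.

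At stake is the interpretation of a listed endpoint. An infant figure about half the adult one could be taken as faster antibody removal when much of the difference is growth. Growth slows with age, so the two doses in arms 6/6b would give different half-lives even if the antibody were handled identically.

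**Working it through.** The article states no expected infant half-life or clearance, so there is no figure of its own to reproduce.

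**Inputs from the article.** Dosing within 96 h of birth; windows of 6 months (arms 1–5), and 3 months then 6 more (arms 6/6b); adult half-lives of more than 3–4 and 4–6 months.

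**Assumptions not in the article.** Volume proportional to weight; weight doubling in 4–6 months early on and 8–12 months later; clearance per unit volume constant.

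**Half-life, closed form.** Let k = ln 2/T be the elimination rate (true half-life T) and g = ln 2/G the growth rate (weight-doubling time G). With V(t) = V0·exp(gt), the amount falls as exp(−kt) and the concentration as exp(−(k+g)t). Hence

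apparent half-life = 1/(1/T + 1/G).

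| True T (months) | G = 4 | G = 5 | G = 6 |
|---|---|---|---|
| 2 | 1.33 | 1.43 | 1.50 |
| 4 | 2.00 | 2.22 | 2.40 |
| 6 | 2.40 | 2.73 | 3.00 |

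For T = 4 and G = 5: 1/(0.25 + 0.20) = 2.22 months. Across G = 4–6, T = 4 reads 40–50% short. At G = 8–12 the same T = 4 reads 2.67–3.00 months, which is why the two doses would differ.

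**Sensitivity to volume scaling.** If volume grows as weight to the power b, the formula becomes 1/(1/T + b/G). For T = 4 and G = 4–6, an illustrative b = 0.75 gives 2.29–2.67 months and b = 0.5 gives 2.67–3.00. The bias shrinks but keeps its sign.

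**Numerical check with absorption and visit times.** One compartment, subcutaneous absorption rate 0.3/day, volume 80 mL/kg, clearance and volume both proportional to weight, sampling at the clinic visits in Tables 4 and 5, terminal slope from day 28. Assumed weight ratios to birth are 1.6–2.0 at 3 months and 2.0–2.5 at 6 months.

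| True half-life (days) | Arms 1–5, 6 months | Arm 6 dose 1, 12 weeks |
|---|---|---|
| 90 | 56–61 | 45–54 |
| 120 | 66–74 | 52–63 |
| 180 | 81–93 | 60–77 |

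That is 32–55% too short over 6 months and 40–66% over 12 weeks. With growth switched off, the same analysis recovers the true value within about 1%.

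**Clearance.** By mass balance, the integral of CL(t)·C(t) equals the absorbed dose, so absorbed dose/AUCinf is the exposure-weighted mean of CL(t), whatever volume does. In the model above (dose fully absorbed), CL(t) = k·V0·exp(gt). Its exposure-weighted mean is k·V0·(1/k)/(1/(k+g)) = (k+g)·V0, and dose/AUCinf is also (k+g)·V0. The two agree exactly, so dilution does not bias clearance. Error enters only if the extrapolated tail is wrong or if clearance is scaled to birth weight. In the numerical check for arms 1–5, tail extrapolation put CL/F about 6–23% above the exposure-weighted mean when clearance grows as weight, and about 10–36% above when it grows as weight to the power 0.75.

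**The case against.** The strongest reply is that the dosing interval depends on how long plasma concentration stays above target in a growing infant. A half-life that includes growth describes that decline, and the proportion of infants above IC80 is listed as an endpoint in its own right. A growth-corrected half-life used alone would overstate how long cover lasts. This stands: the non-compartmental half-life is a valid description of concentration decline at the ages studied, and C_max, AUClast and the proportion above target are observed quantities that growth does not bias. What is wrong is reporting it as elimination half-life.

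A reader might also infer that clearance is overstated. In the closed-form model, dose/AUCinf divided by clearance at birth is (k+g)/k, about 1.3–2.0 for half-lives of 2–4 months and G = 4–6. The article does not support reading this as bias. The ratio reflects real growth in clearance as the infant grows, and nowhere is clearance at birth named as the target or scaling to birth weight prescribed.

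Three further objections have partial force. The article plans no formal comparison with adults or between doses, so the misreading is a risk and not a planned analysis. The sizes rest on growth assumptions from outside the article; the direction does not. And the full protocol or analysis plan, not shown, may add a population model. The article nevertheless commits to non-compartmental analysis without qualification.

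**Conclusion.** The point holds for half-life. The planned method does not estimate the elimination half-life that the endpoint names; it estimates an apparent concentration half-life that combines elimination and growth. With volume proportional to weight and doubling in 4–6 months, a true 4-month half-life reads as 2.0–2.4 months, and less if growth over the first 12 weeks is faster than that. Slower growth or less-than-proportional volume gives a smaller gap. If clearance rises more slowly than volume, elimination half-life itself lengthens with age and no single figure describes it, which is a further reason for a model.

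The half-life should therefore not be set beside adult figures, nor dose 1 beside dose 2, without correction. The point does not extend to a dilution bias in clearance, to C_max, AUClast or the proportion above target, or to the primary safety endpoint. It is an inexpensive improvement to one descriptive secondary endpoint.

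**What to change.** 1. Keep non-compartmental analysis for C_max, AUClast and clearance, and label the last as apparent clearance (CL/F), since all dosing is subcutaneous.
2. Report the non-compartmental half-life as an apparent concentration half-life, including growth.
3. Add a supportive population PK model for each antibody, pooling its arms, with body weight at each visit as a time-varying covariate on clearance and volume. Take elimination half-life and growth-adjusted clearance from this model, and show how they change under other weight exponents.

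Pooling gives at most 32 infants for CAP256V2LS (arms 1, 2, 3 and 6: 4 × 8) and 24 for VRC07-523LS (arms 4, 5 and 6: 3 × 8). No new blood samples are needed. The costs are some modelling work and a paragraph in the analysis plan, results that lean on an assumed weight relationship in few infants, and a weight recorded at every PK visit. The schedules list a clinical exam at each visit but do not state that weight is taken.
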